**Table 1 T1:**
[figure not shown]
Dosimetric parameters proposed for the study.

It is considered that this study has minimal risks since, considering the hypothesis of BP reduction due to vasodilatation caused by photobiomodulation, subjects may present BP decrease with possible presence of clinical signs such as lipothymia, vertigo, complaint of malaise by the patient. If this happens, therapy will be stopped immediately and Trendelenburg maneuvers will be performed to increase venous return and BP.

### Analysis and publication of data

2.9

After data collection, the data will be grouped into categories using Microsoft Office Excel 2007 (Redmond). The data will be analyzed using descriptive and inferential statistics and compiled into tables and/or graphs with the help of SPSS version 24.0 (IBM, New York). If the data are normal, parametric tests will be used to test inter and intragroup differences.

If they are not normal, nonparametric tests will be used. The level of significance adopted for all tests will be α = 0.05. The data will be protected in a spreadsheet and in a cloud under the care of the researchers. After the study, the same will be presented for publication in the form of a scientific article, where readers will have access to the results obtained in this research.

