### Sample size

2.3

The determination of the number of patients necessary was calculated using G ∗ Power software (version 3.1.9.2, Franz Faul, Universität Kiel, Germany), in which the values for the mean and standard deviation of the primary outcome variable (systolic or diastolic BP) came from the article by Pereira et al.^[21]^ The calculation was performed using the ANOVA repeated measures, with a significance of 5% and power of test at 95%. According to sample calculation, 44 hypertensive patients will be divided into 4 groups with 11 individuals each.

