### Group composition and randomization: (recruitment and randomization)

2.6

Recruitment will be carried out respecting Resolution 466/2012, which regulates human research in Brazil. The patients recruited will have their multiprofessional charts analyzed for demographic and descriptive characterization of the sample.

Nursing consultations in the form of a home visit, or not—at the discretion of the participant, will be scheduled to give healthcare guidance, for an initial interview, completion of the clinical file, and realization of hemodynamic and anthropometric measurements, as well as blood collection and photobiomodulation interventions.

For the application of the photobiomodulation, the participant will place a bracelet where the tip of the coupled laser equipment will be positioned on the radial artery.

We will use the randomization mechanism provided by Sealed Envelope Ltd. (London, UK)^[22]^ Participants will be randomized into blocks of 8 individuals, comprising 4 study groups. They will be identified by sequential numbers, according to the order of recruitment. Immediately before starting treatment, the researcher will look at the randomized list and, using their identification number, verify which group the participant belongs to. The patient will not know to which group he or she has been allocated; only the researcher who will do the irradiations will know. The analysis of the data will be performed by a third person who will also not know group allocations.

A schematic diagram of time schedule of enrolment and interventions of the research groups is summarized in Figure 1.

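### The BP test is chosen by whether the data look normal, is not tied to the model used for sample size, and no baseline-adjusted group comparison is stated, with 11 patients per arm

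*Protocol article*

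**What the plan says.** Section 2.9 (Analysis and publication of data) sets a two-branch rule. The first branch is "If the data are normal, parametric tests will be used to test inter and intragroup differences". The second is "If they are not normal, nonparametric tests will be used". It names no test in either branch and does not say how normality is judged, or on what (raw values, changes or residuals). On the threshold it adds "The level of significance adopted for all tests will be α = 0.05".

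Section 2.3 (Sample size) rests on a specific model: "The calculation was performed using the ANOVA repeated measures", at 5% significance and 95% power, giving "44 hypertensive patients will be divided into 4 groups with 11 individuals each". It leaves the primary variable open as systolic or diastolic BP.

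Section 2.7 (Outcomes) has BP measured before, during and after every session and again at follow-up, so a pre-treatment value exists for everyone. Section 2.6 describes allocation as "Participants will be randomized into blocks of 8 individuals, comprising 4 study groups" and mentions no stratification by BP.

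**The concern.** A rule that picks the test from the observed data leaves the primary analysis unfixed until the data are seen. The two branches can also answer different questions: a t test or ANOVA compares means, while a rank test compares distributions. Which question gets answered would depend on a normality check in samples of 11, where such checks are weak. If the second branch is taken, the trial may leave the model that justified 44 patients.

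The second strand is baseline BP. In arms of 11, chance differences in starting BP are common. A between-group comparison that does not condition on the starting value carries part of that difference into the result, and it is less precise than the data already being collected would allow.

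**Working it through.** **The plan's own figure.** The total of 44 can be neither confirmed nor refuted, because section 2.3 prints no mean, SD, effect size, number of measurements or correlation. With an assumed correlation of 0.5 between measurements and 2 to 7 measurements, 95% power at 44 needs an effect size f of 0.57 down to 0.50 for a between-group test, 0.28 down to 0.19 for a within-group test, or 0.33 down to 0.23 for the interaction. Which effect was powered is therefore unknown. Section 2.9 does not settle it, since it does not name the model.

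**Reliability of the normality check at n = 11** (5% Shapiro-Wilk test assumed, one check per group)
- Four truly normal groups, at least one flagged: 1 − 0.95^4 = 0.185.
- Two truly normal groups, at least one flagged: 1 − 0.95^2 = 0.098. In simulated two-arm trials the rule switched to the rank test in 10%.
- Power to detect a lognormal sample with sigma 0.5: 0.28 (simulated).
- Two arms with lognormal errors: the rule switched in only 24-41% of simulated trials.

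**Chance imbalance in baseline BP**
- SD of the difference between two arm means: √(2/11) = 0.426 SD.
- P(|difference| > 0.5 SD): 0.5/0.426 = 1.17, two-sided P = 0.24.
- At least one of the two laser-placebo pairs: 1 − (1 − 0.241)^2 = 0.42.

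**Error rate of the two-stage rule** (8,000 simulated trials per setting, 11 v 11, Shapiro-Wilk in each arm, then t or Mann-Whitney, no true effect, ρ = 0.5 or 0.7)
- Overall: 0.051-0.053 with normal data and 0.051-0.056 with lognormal errors. The Monte Carlo standard error is √(0.05 × 0.95/8000) = 0.002, so there is no material inflation.
- Among trials with baseline imbalance above 0.5 SD (normal data):

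| ρ | Two-stage, post value | Two-stage, change | ANCOVA |
|---|---|---|---|
| 0.5 | 0.095 | 0.106 | 0.056 |
| 0.7 | 0.148 | 0.078 | 0.049 |

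**Precision for one laser-placebo pair.** The baseline/follow-up correlation ρ is not in the document and is assumed. Variances are relative to a post-value comparison, which is set to 1. The change score is 2(1 − ρ). ANCOVA is (1 − ρ²) × 20/19, where 20/19 is the small-sample penalty for estimating the slope. Power is for an assumed true difference of 1 SD, two-sided 5%.

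| ρ | Change | ANCOVA | ANCOVA v post | ANCOVA v change | Power: post / change / ANCOVA |
|---|---|---|---|---|---|
| 0.3 | 1.40 | 0.958 | −4% | −32% | 0.61 / 0.47 / 0.62 |
| 0.5 | 1.00 | 0.789 | −21% | −21% | 0.61 / 0.61 / 0.71 |
| 0.7 | 0.60 | 0.537 | −46% | −11% | 0.61 / 0.82 / 0.86 |
| 0.8 | 0.40 | 0.379 | −62% | −5% | 0.61 / 0.94 / 0.95 |

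At ρ 0.5 to 0.7 the gain over change scores is equivalent to 1/0.789 = 1.27 down to 0.60/0.537 = 1.12, or 27% down to 12% more patients.

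**Limit of the gain.** With lognormal errors and a 1 SD difference, simulated power for the two-stage test on change against ANCOVA was 0.76 v 0.78 at ρ = 0.5, but 0.93 v 0.87 at ρ = 0.7.

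**The case against.** The strongest reply is that a condensed article commonly leaves named tests and covariates to a fuller protocol or analysis plan, which is not shown. That stands for the silence on covariates taken alone. It does not cover the normality rule, which is stated text and would have to be replaced, not merely filled in.

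A reader might infer that the plan makes no use of baseline BP. The document does not support that. The within-group tests in section 2.9 would naturally draw on pre-treatment values, and a repeated-measures ANOVA as in section 2.3 would normally carry baseline as one time level. What can be said is only that no baseline covariate or adjusted between-group comparison is stated. Treating baseline as a time level does not remove the point: with one follow-up time, the group-by-time contrast is a change-score comparison, which remains sensitive to imbalance.

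A reader might also infer that the rule inflates false positives, or that unstratified randomisation is a defect. Neither holds. Overall error is about 5%, because randomisation already accounts for chance imbalance on average; error rises only among trials that happen to be imbalanced. A false alarm also costs little power: with normal data and a 1 SD difference at ρ = 0.5, simulated power was 0.60 for the t test and 0.57 for Mann-Whitney.

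Nor can one say that the second branch could not address group-by-time. No rank test is named, and a rank test on change from baseline does compare change between groups.

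Finally, the larger 21-46% saving is measured against a post-only analysis that the plan never states. The comparison with change scores is the fairer one.

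**Conclusion.** The point holds in a limited form. Section 2.9 lets an unreliable normality check choose between unnamed tests, is not linked to the section 2.3 model, and states no baseline-adjusted comparison of BP between groups. The consequences are a primary test and estimand that depend on the data, exposure to baseline imbalance (a gap above 0.5 SD in about 24% of trials for a given pair, 42% for at least one of the two pairs), and lost precision of about 11-21% in variance against change scores.

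The precision figures rest on an assumed ρ of 0.5 to 0.7, near-normal errors and a single 11 v 11 comparison. Against change scores the gain shrinks as ρ rises, and it is not guaranteed with strongly skewed errors. This is an improvement the sponsor should make, not an error that invalidates the trial.

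**What to change.** For the primary outcome, replace the normality rule in section 2.9 with one prespecified model:
- Name the BP variable, since section 2.3 leaves systolic or diastolic open, and the time of the primary comparison.
- Fit either an ANCOVA at that time, or a linear mixed model with group, time and group-by-time, with BP before the first session as covariate in both cases.
- Report the adjusted laser-placebo difference with its 95% CI.
- Keep a rank-based analysis as a sensitivity analysis only. It also covers the skewed case in which ANCOVA may lose power.
- Restate section 2.3 for the same model and the same effect, with its inputs.

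The data are already planned. The cost is about one degree of freedom, a change of analysis wording and a restated sample-size paragraph.

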## Discussion

3

Studies have demonstrated, both in vitro and in vivo, the control of inflammatory process and oxidative stress, as well as the production of NO with vasodilator and angiogenic action. Therefore, LILT can biomodulate factors that are closely related to endothelial dysfunction. ^[23–26]^

In a study carried out with sublingual laser application in hypertensive pregnant women, Madi^[27]^ observed that systemic vascular resistance and, consequently, systolic, diastolic, and mean arterial pressure, suffered a statistically significant decrease following photobiomodulation.

Weber et al^[28]^ described the different effects and mechanism of action of ILIB, including: anti-inflammatory effects that improve the immunological activity of blood; positive influence on rheological properties of the blood including vasodilatation, decreasing aggregation of thrombocytes, and a better deformability of the erythrocytes, thus resulting in a better supply of oxygen and with that a decrease in the partial pressure of carbon dioxide, such findings being relevant for the healing of wounds; improvement of hypoxia and tissue normalization with an increase in the synthesis of ATP occurring with the normalization of the cellular membrane potential; as well as effects of increased NO release from monocytes.

In Russian university clinics the use of intravascular irradiation is used to avoid thromboembolic complications and to improve the healing of postoperative wounds, bringing together the analgesic, spasmolytic, and sedative effects specific to the laser. There are additional reports of the benefits of such therapy in cases of chronic glomerulonephritis, for the improvement of inflammatory parameters in acute pyelonephritis and necrotizing pancreatitis, as well as the use of ILIB in obstetrics and gynecology to stimulate uteroplacental blood exchange and as a prophylaxis and therapy for inflammation of internal genitalia. ^[28]^

Despite promising results, clinical studies with an adequate level of scientific evidence are needed to fill the gap found in regards to the effects of systemic irradiation. Thus, it is expected that the present work will contribute to the scientific community, providing the first step to understanding the systemic effects caused by irradiation of the radial artery during the treatment of hypertension.
